##### Novel biomarker development

We re-analyzed expression data from a large transcriptomic study (n = 491); there are significant gains in sensitivity when increasing from 10 to 30 samples within groups, and only a moderate benefit of increasing from 30 to 40 in each group [49]. Specificity requires fewer samples, as it stops improving significantly after 20 samples per condition. Thus, these results justify our sample size of 30 per study arm.

##### Immunologic analyses

In our preliminary work, we used a bootstrap approach to estimate the expected estimation error for the AUC, sensitivity, and specificity for our T cell markers at our proposed training sample size (n = 30). We expected to be able to estimate the AUC within 0.10, the sensitivity within 0.17, and the specificity within 0.13 using single markers alone. We fully expect that combination biomarkers will lead to more accurate estimates (the combination marker accuracy cannot be estimated because our preliminary data lead to perfect predictions). However, the single marker predictions demonstrate that our sample size is large enough to estimate these quantities with sufficient accuracy.

### Statistical analyses

#### Mtb killing, cytokine analyses, and cellular immune responses

For the Mtb killing (intracellular bacterial growth) assays, we will log-transform relative luminescence units and compare groups using ANOVA including nutrition status, parasite status, gender and any other significant covariate using a forward selection approach. For all analyses, if needed (e.g. skewed or bimodal data), we will apply a non-parametric Kruskal–Wallis test. For colony forming unit measurements, we will use a Poisson regression model that includes covariates using a forward selection approach. For cytokine analyses, markers will be compared using ANOVA or Kruskal–Wallis test. If needed, to correct for multiple comparisons, we will apply a Bonferroni adjustment. To understand the effect of parasite treatment and nutritional supplementation over time, we will use time-course repeated measurements on the same individual and a mixed linear model.

The predictive value will be evaluated by receiver operating characteristics (ROC) curve analysis and logistic regression modeling using covariate metadata. Because our preliminary data demonstrate a strong signal from these markers, we will split our cohort into a training set (n = 20 in each group) and a test set (n = 10 in each group) for cross-validation purposes. The markers will be evaluated for their predictive abilities individually, as well as in combination. The combination logistic regression biomarker will be selected using a forward-step approach, adding markers one at a time and evaluating the predictive value (cross-validation within the training set).

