### Study population

Study staff identify new TB index cases (ICs) through the National Tuberculosis Elimination Programme (NTEP). Inclusion criteria are: (1) Age ≥ 18 years; (2) New sputum-smear positive (≥ 1+ acid fast bacilli [AFB]) pulmonary TB that is culture or GeneXpert positive; (3) No history of TB treatment; (4) Have at least one household contact (HHC) with whom they shared a house during the previous month; (5) Agree to have HHCs contacted. Exclusion criteria include: (1) Pregnant; (2) No GeneXpert or culture confirmation and unable to provide sputum sample; (3) No HHCs; (4) Known MDR or XDR TB; (5) BMI < 14 kg/m^2^ as to avoid refeeding complications; (6) Kwashiorkor, lower extremity edema or lower extremity neuropathy in those with BMI < 14.

Inclusion criteria for HHC include: (1) Age 18–60 years; (2) Housemate of an eligible TB case for at least the past month; (3) HIV seronegative or willing to be tested; (4) Willing to be tested for pregnancy. Exclusion criteria include: (1) Pregnant at enrollment; (2) Having known diabetes mellitus or evidence by hemoglobin A1C (HbA1c) > 6.5%; (3) GeneXpert positive among those able to produce sputum; (4) History of TB disease; (5) Karnofsky score ≤ 10 (moribund); (6) If BMI < 16 kg/m^2^, abnormal potassium, magnesium, or phosphorus; (7) Kwashiorkor; pitting edema; neuropathy [23].

All HHCs in the home are approached for enrollment. All eligible household contacts in one house are enrolled for prospective follow up if the HHCs fall in overlapping study arms. If there are more than one eligible HHCs, but no overlapping study arm designations, any malnourished HHC screened is enrolled to limit selection bias. We expect to enroll 760 HHCs to identify 120 study participants for longitudinal follow-up. Sample size was determined by participant data from the Regional Prospective Observational Research for Tuberculosis (RePORT India) cohort study [24].

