### Two-month repeat QFT-plus

For any malnourished or parasite positive participant with a negative or indeterminate QFT-Plus result during screening, a follow up visit is conducted approximately 2 months later for repeat QFT-Plus. Any HHC positive upon repeat testing is enrolled for longitudinal follow up. For those who are malnourished, still QFT-Plus negative upon repeat testing, but have a HHC already enrolled into the intervention due to malnutrition, the participant is enrolled into the study for longitudinal follow up.

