### Nutritional intervention

Undernourished participants are re-consented and enrolled into the study intervention (food and micronutrient supplementation) for 6 months followed by an additional 18-months of extended follow-up. In order to encourage adequate nutritional intake, even in the context of food sharing, the nutrition intervention food rations provided are sufficient to feed all household members. At enrollment, participants are asked the number and age of household members.

The kcal requirements for the food supplements were derived from the Indian TB Nutrition Guidelines that men and women require 2500 and 2100 kilocalories (kcal) respectively; thus, HHCs receive 2600 kcal each with children 13 years and younger receiving 1300 kcal [39]. The 2600 kcal/day needs were determined based off clinical feeding guidelines of 35–40 kcal/kg for undernourished patients [40] to achieve a BMI level considered optimal (21 kg/m^2^) based on the National Institute of Nutrition (NIN) in India’s recommendation for optimizing health and nutrition. In order to determine the contents of the food ration, we consulted local partners, TB experts in India, and nutritionists to create a meal package that is locally acceptable, suitable for vegan and omnivores, and that gives participants dietary variety without compromising nutritional quality. The meal package is comprised of pulses, white rice, groundnuts, and oil; nutrition calculations were made from standard nutrient analysis based on the *Exchange Lists for Meal Planning*, by the Academy of Nutrition & Dietetics in conjunction with the American Diabetes Association [41] (Table 1). These foods were also selected because they can be easily transported to the participant homes and they do not require refrigeration. Enrolled participants also receive a multiple micronutrient supplement (Life-Extension Two-Per-Day Tablets) [42] which contains over 100% of the RDA for Vitamins A, B6, B12, C, D3, and E.

**Table 1 Tab1:** Tuberculosis: Learning the Impact of Nutrition (TB LION) nutritional intervention package for one adult per day

Food category	Food item	Kilocalories	Protein (g)	Fat (g)
Fat (5 g/day)	Vegetable oil	45	0	5
Pulse (117 g/day)	Red gram, green gram, and black gram	468	23.4	1.5
Grains (325 g/day)	White rice	1301	22.75	2.3
Nuts (143 g/day)	Ground nuts	786	35.75	70.1
Total		2600	81.9	78.8

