The field team visits households every other week to replenish the food, assess food consumption and changes in participant health. During the initial food delivery visit, nutritionists provide study food containers and then weigh each container, taring the scale to accurately account for the weight of container. They then add the calculated amount of each food item and mark each container with a black marker to indicate the fill line. The weight of each respective food container is recorded. Nutritionists return to the household every 2 weeks to evaluate the remaining food and vitamin supplement. The remaining food (for each item) is poured into a tared tray, weighed and recorded. Using the initial calculated food quantity and remaining quantity, nutritionists calculate the amount of food consumed by the household and the amount required to replenish the stock which is added to the container before the remaining food to minimize food expiry.

Severely undernourished participants (BMI 14–16) receive partial supplementation for the first 2 weeks of intervention; 30% for the first week and 50% the second week. By the third week, participants will receive 100% of the supplementation. Study staff assess electrolytes (potassium, magnesium, and phosphorus) and conduct an assessment for food consumption and changes in participant health before replenishing the week’s food supply. If electrolyte results are normal, food supply is increased; however, if food is not being consumed based on observation, a second week of the partial ration is provided and electrolytes re-checked. If electrolyte results are abnormal, food supplementation is stopped, and the participant is referred to the hospital. HHC bi-weekly visits detailed above will begin once 100% of the ration is received.

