#### RNA sequencing

RNA will be extracted from our samples and sequencing libraries will be prepared and sequenced on an Illumina sequencer as described in our previous work [50, 51]. We will perform transcriptomic analysis to understand mechanisms of immune modulation by undernutrition and parasitic infections. Data will undergo quality control, aligned to the most recent human reference genome (hg38) using RSubread, and feature counts will be estimated for each gene as in our previous work [50, 51]. We will use the edgeR package to determine differential gene expression based on a false discovery rate cutoff of 0.05. The data will be subjected to the following: (i) Transcriptional modular/network analysis; (ii) GSVA and ssGSEA scoring of multiple existing TB-related gene expression pathways using our TBSignature profiler (https://github.com/compbiomed/TBSignatureProfiler); and (iii) Ingenuity pathway analysis [51]. We will use the differentially expressed gene sets and/or existing biomarker genes to derive a logistic regression model to develop biomarkers of Mtb infection in undernourished HHC and see if these predict TB risk. To address response to nutritional supplementation and parasite treatment, we will apply a mixed model using the dream R package [52] to account for the repeated measures analysis. We will use an FDR threshold of 0.05 to control for multiple comparisons.

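### Housemates are enrolled together, but no stated analysis allows for household clustering, so standard errors for the group contrasts are wrong (probably too small, by a modest and uncertain amount)

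*Protocol article*

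**What the plan says.** **Enrolment.** Under Study population, the article states that "All eligible household contacts in one house are enrolled for prospective follow up if the HHCs fall in overlapping study arms". Where the arms of eligible housemates do not overlap, "any malnourished HHC screened is enrolled to limit selection bias". Under Two-month repeat QFT-plus, a malnourished contact who is still QFT-Plus negative is also followed if they "have a HHC already enrolled into the intervention due to malnutrition".

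**Intervention.** Under Nutritional intervention, "the nutrition intervention food rations provided are sufficient to feed all household members". At the two-weekly visits the nutritionists "calculate the amount of food consumed by the household", so both supply and measured consumption are household quantities.

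**Analysis.** Under Mtb killing, cytokine analyses, and cellular immune responses, the plan is to "compare groups using ANOVA including nutrition status, parasite status, gender and any other significant covariate using a forward selection approach". Kruskal–Wallis is the fallback, Poisson regression serves colony counts, and logistic regression with a 20/10 training/test split per group serves prediction. For effects over time, "we will use time-course repeated measurements on the same individual and a mixed linear model". Under RNA sequencing, edgeR is used for differential expression, and for response to supplementation and parasite treatment "we will apply a mixed model using the dream R package", given there as the way to handle repeated measures. Participant data are analysed by regression and ANOVA. None of these sections, nor the sample size section, mentions the household.

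**The concern.** Enrolled housemates share an index case, and with it exposure, and a home environment. After supplementation starts they also share a ration. Positive within-household correlation of immune and transcriptomic outcomes is therefore the natural expectation. Ordinary ANOVA, Kruskal–Wallis, Poisson, logistic and edgeR analyses treat people as independent, and a mixed model with only a person effect treats different people in one house as independent.

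The nutrition contrast is central to the aims on undernutrition and supplementation. If enrolled housemates have the same nutrition status, nutrition behaves partly as a household-level factor. Its standard error is then understated and false positives exceed the nominal rate. Separately, a training/test split made person by person could put housemates on both sides, so the test set would not be fully independent of the training set.

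**Working it through.** **The plan's own figures.** Four arms of 30 give 4 × 30 = 120, that is 60 versus 60 on nutrition. The yield is 120/760 = 15.8%. The sample size of 30 is justified by earlier studies, a reanalysis and a bootstrap, with no power formula to reproduce. The stated AUC precision of 0.10 is close to what independent subjects would give: the Hanley–McNeil 95% half-width at 30 versus 30 is 0.113, 0.099 and 0.082 for AUC 0.80, 0.85 and 0.90. No visible margin is left for clustering.

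**Formulas.** Design effect DE = 1 + (m − 1) × ICC, with m the (size-weighted) number of enrollees per household. Effective n = n/DE. Actual two-sided error at nominal 5% = 2 × [1 − Φ(1.96/√DE)]. These hold when housemates are on the same side of the contrast.

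**Scenario A: tied to the stated yield.** Take p = 0.158 from the article. Assume k = 2 to 5 contacts screened per house, each selected independently.

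- Mean enrollees in houses with at least one: kp/[1 − (1 − p)^k] = 1.09 (k = 2) to 1.37 (k = 5).
- Size-weighted m = 1 + (k − 1)p = 1.16 to 1.63.
- Lowest case: DE = 1 + 0.158 × 0.1 = 1.02, effective n 60/1.016 = 59, error 5.2%.
- Highest case: DE = 1 + 0.632 × 0.3 = 1.19, effective n 60/1.189 = 50, error 7.2%.

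**Scenario B: eligibility aggregates in households.** Assume every house supplies m enrollees, all in one arm. The simulation is the 2 × 2 ANOVA with 30 per cell, no true effect and 20,000 runs.

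| m | ICC | DE | Effective n of 60 | Error, formula | Error, simulated |
|---|---|---|---|---|---|
| 2 | 0.1 | 1.10 | 54.5 | 6.2% | 6.3% |
| 2 | 0.3 | 1.30 | 46.2 | 8.6% | 8.9% |
| 3 | 0.1 | 1.20 | 50.0 | 7.4% | 7.3% |
| 3 | 0.3 | 1.60 | 37.5 | 12.1% | 12.7% |

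If only the undernourished come in pairs, the simulated error is 5.8% to 6.8% at ICC 0.1 to 0.3.

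**Scenario C: housemates straddle the contrast.** With pairs of one undernourished and one well-nourished housemate, the simulated error falls to 3.9% at ICC 0.1 and 2.0% at ICC 0.3. The test is then conservative.

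**Change over time.** A constant household intercept drops out of each person's change from baseline. A simulated before–after test in 30 pairs of housemates with such an intercept gave 4.9%. Only correlation of the changes themselves, for example through a shared ration, would understate that standard error. A household intercept does not model it.

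**The case against.** The strongest reply has four parts.

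1. **The article is condensed.** It names model families and does not say that errors are independent, and random-effect structure is often left to the SAP. It stands that a fuller document may already include a household term. But the article does choose its tests and says what its mixed models are for. It recognises dependence within a person and not the dependence its own enrolment rule creates. Followed as written, the plan ignores the household.

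2. **The direction is not fixed.** A reader might infer that p-values for the nutrition contrast are certainly too small. The document does not support that, because overlapping arms are not defined. Undernourished and well-nourished contacts who both carry parasites could count as overlapping, and such housemates would straddle the contrast. The rule favouring malnourished contacts, and the extra enrolment of malnourished QFT-Plus negative housemates, make the same-side case more likely but not certain.

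3. **The size may be small.** A reader might infer error rates of 12%, or about 17% at ICC 0.5. Those need about three enrollees in every house, which sits badly with a 15.8% yield unless eligibility aggregates strongly within households.

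4. **The ration is not a baseline matter.** A reader might tie the shared ration to every nutrition comparison. It cannot affect the baseline ANOVA, where any correlation comes from shared exposure and environment. It bears only on analyses after supplementation begins.

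Parts 2 to 4 stand and limit the claim. The study's exploratory label lowers the stakes, but it does not make a wrong standard error acceptable.

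**Conclusion.** The point holds in limited form. The enrolment rules create household clusters and no stated analysis allows for them, so standard errors for the group contrasts are wrong whenever within-household correlation is not zero. With positive correlation they are probably too small, but they would be too large for housemates who straddle the nutrition contrast.

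The best-anchored estimate is an actual error of about 5% to 7% at nominal 5%. It rests on the stated yield, an assumed 2 to 5 contacts screened per house, independent selection, same-side housemates and an assumed ICC of 0.1 to 0.3. Aggregation of eligibility in households would raise it, to about 12% at three enrollees per house and ICC 0.3. For supplementation and parasite-treatment effects no inflation is shown; the risk there depends on housemates' changes being correlated. Leakage between training and test sets is possible because no allocation rule is given, but its size was not estimated.

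**What to change.** - **Baseline arm comparisons:** add a household random intercept or use household-clustered standard errors. For RNA-seq, use dream with household as a random effect, or an equivalent method. Where a rank test is the fallback, use a form that respects households.
- **Supplementation and treatment effects:** besides the participant effect, add a household-by-time term or use household-clustered errors. A household intercept alone is not enough.
- **Prediction:** assign whole households to the training or test set and to cross-validation folds.
- **Reporting:** define what counts as overlapping arms, and report the number of enrollees per household and the estimated ICC.

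The cost is analysis-plan wording and a little more programming. Household membership is already known from enrolment, so no new data are needed. If housemates are mostly on the same side, intervals become slightly wider.

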### Study expectations

In this study, we hypothesize that in HHC of adults with active TB, undernutrition and parasitic infection increase the risk of progression to TB disease and alter the immune response. Further, we hypothesize that nutritional supplementation and treating parasitic infections reverse their effect on the immune response. We anticipate observing that undernutrition and parasitic infection are independently and jointly associated with reduced Mtb killing, increased Th2 and Treg response, and TB risk signatures. We expect that nutritional supplementation improves Mtb killing, increase Th1 response, and alters TB risk signatures. Lastly, we anticipate that treating parasitic infection results in the normalization of immune parameters and the resolution of TB risk signature risk.

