## Discussion

The TB LION study allows us to assess an overlooked obstacle for TB elimination in India—undernutrition—and to evaluate the potential role for parasitic infections in the Indian context. There is a paucity of studies that have assessed the impact of undernutrition on the immune response during Mtb infection and more importantly whether these can be reversed with interventions. The TB LION study, with its ample macronutrient and micronutrient supplementation, rigorous monitoring of nutritional intake, and detailed immunologic analyses address these barriers.

One strength of the study is that we address how the impact of undernutrition is modulated by parasitic infections that are common in India. Intestinal parasites can decrease absorption of key macronutrients (e.g., protein) and micronutrients (e.g., zinc) [21]. Parasites may also have a direct effect on risk of TB progression by inducing Th2 responses and weakening Th-1 (and Th17) responses needed to control Mtb [53]*.* Antihelminth treatment in persons with Mtb infection and Schistosoma or Strongyloides coinfection is associated with increased CD4^+^ IFNγ^+^  cells, suggesting improvement in immune response [54], but data are needed to address whether the implications are similar for other parasites. The TB LION study further informs the role of parasitic infection on risk of progression to TB disease, the time course of improvement in these responses after parasite treatment, and the durability of the response. Furthermore, we are able to address the interplay of undernutrition and parasite infections.

The TB LION study is an ambitious study, with potential to yield very meaningful information. We are confident that our design and methodology, with the addition of sample collection to address the impact of potential COVID-19 infection (through serology), provides comprehensive data to draw sound conclusions regarding the risk of progression to active TB among HHCs. Another key strength of this study is the prospective follow up with clinical assessment on all study participants. Extensive data collection on all participants allows for thorough comparative analyses within and across participant groups. We perform a qualitative assessment of the intervention, a cost-effectiveness analysis of nutritional interventions, and assessments of micronutrient contributions to immune response.

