## Conclusion

TB LION study is novel in that we have integrated epidemiologic, nutritional immunologic and bioinformatics methodologies to assess not only the individual effects of undernutrition and parasitic infection on latent TB infection and risk of progression to TB disease, but also the combined effect of these conditions. This study transcends individual level care and presents the opportunity to benefit the population at large by analyzing factors that affect disease progression potentially reducing the overall burden of people who progress to TB disease.

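### Immune-assay covariates are chosen by significance in non-randomised arms, and no nutrition-by-parasite contrast is specified for the joint effect the trial claims

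*Protocol article*

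**What the plan says.** In the Protocol article, under Mtb killing, cytokine analyses, and cellular immune responses, luminescence is log-transformed and the plan is to "compare groups using ANOVA including nutrition status, parasite status, gender and any other significant covariate using a forward selection approach". Gender is a named term. Every other covariate must be significant to enter. For colony counts, "we will use a Poisson regression model that includes covariates using a forward selection approach". For skewed or bimodal data, in any of the analyses, "we will apply a non-parametric Kruskal–Wallis test". On multiplicity: "If needed, to correct for multiple comparisons, we will apply a Bonferroni adjustment". The RNA sequencing subsection, by contrast, fixes a false discovery rate of 0.05.

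None of the Statistical analyses subsections names a nutrition-by-parasite term or a joint contrast. Yet Study expectations anticipates that "undernutrition and parasitic infection are independently and jointly associated with reduced Mtb killing", the Discussion says "we are able to address the interplay of undernutrition and parasite infections", and the Conclusion presents as novel not only the individual effects "but also the combined effect of these conditions".

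Longitudinal follow-up places contacts in four arms of 30 by BMI and parasite status. Demographics and medical history lists socio-economic status, alcohol, smoking and food insecurity among the data collected, because they may relate to Mtb infection. The Participant data subsection promises adjustment for confounders. It concerns demographic, socio-economic and anthropometric data, gives no list, and does not clearly extend to the assays.

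**The concern.** Undernourished and well-nourished contacts can differ in many ways besides nutrition. Whether a variable confounds that comparison depends on its relation to both nutrition and outcome, not on whether its coefficient passes a significance test in 120 people. A weak confounder often fails the test, is left out, and leaves part of its bias in the nutrition effect. The p-value then also ignores the selection step.

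The fallback makes this worse: the shape of an assay's distribution would decide whether any adjustment is made at all.

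The arms form a 2x2 layout and the stated interest is in how the two conditions act together. Without a named contrast, the analysis that answers this is left open. If only the listed terms are fitted, an effect confined to the doubly affected arm is spread over both single conditions.

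**Working it through.** **1. The plan's own figures.** 4 arms x 30 = 120, as stated. The immunologic justification of n = 30 is estimation error of 0.10 (AUC), 0.17 (sensitivity) and 0.13 (specificity). Read as 95% half-widths, 1.96 x sqrt(p(1-p)/30) gives 0.171 at p = 0.65 and 0.130 at p = 0.845. The Hanley-McNeil formula with 30 v 30 gives 0.099 at AUC 0.85. The figures are therefore attainable, but the article does not state the underlying values. It gives no effect size, SD, alpha or power for the ANOVA, so nothing here bears on a main effect or an interaction.

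**2. Forward selection.** Simulation of the 2x2 design, 30 per cell, with nutrition, parasite and gender always in the model. Assumed, since the article gives none of these: entry at two-sided 0.05, residual SD 1, no true nutrition effect, confounders with within-group SD 1. Omitting a confounder gives bias = group difference x slope (for example 0.5 x 0.2 = 0.10 SD).

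One confounder, 4,000 runs:

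| Group difference (SD) | Slope | Selected | Bias if omitted | Bias, forward selection | Type I error, forward selection | Type I error, forced in |
|---|---|---|---|---|---|---|
| 0.50 | 0.2 | 55% | 0.10 | 0.025 | 6.3% | 4.7% |
| 0.75 | 0.2 | 57% | 0.15 | 0.035 | 8.3% | 5.4% |
| 0.50 | 0.3 | 88% | 0.15 | 0.010 | 5.7% | 4.9% |
| 0.75 | 0.3 | 89% | 0.225 | 0.009 | 6.2% | 4.4% |
| 0.50 | 0.4 | 99% | 0.20 | about 0 | 5.1% | 5.1% |

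Four confounders, each differing by 0.5 SD and acting in the same direction, 1,500 runs:

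| Slope | Mean number selected of 4 | Bias unadjusted | Bias, forward selection | Type I error, forward selection | Type I error, forced in |
|---|---|---|---|---|---|
| 0.15 | 1.4 | 0.30 | 0.12 | 14% | 5% |
| 0.20 | 2.2 | 0.40 | 0.11 | 13% | 5% |
| 0.30 | 3.5 | 0.60 | 0.03 | 9% | 5% |

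**3. Fitting only the listed terms.** Suppose the true cell means are UP = 1 and U = WP = W = 0 (in SD). Least squares on nutrition and parasite alone gives intercept -0.25 and 0.5 for each factor. The fitted UP mean is -0.25 + 0.5 + 0.5 = 0.75. Read as simple effects, U-W and WP-W would each be 0.5 when both are truly 0.

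**4. Precision of the interaction.** The difference of differences has SE = SD x sqrt(4/30) = 0.365 SD. At two-sided 5% and 80% power the multiplier is 1.960 + 0.842 = 2.802, so the detectable interaction is 2.802 x 0.365 = 1.02 SD. For a main effect (60 v 60) it is 2.802 x sqrt(2/60) = 0.51 SD. Power for an interaction of 0.5 / 0.75 / 1.0 SD is 28% / 54% / 78%. Reaching 80% would need 126 / 56 / 32 per cell.

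**5. Multiplicity.** Evaluation of antigen-specific memory T-cells names four memory subsets and three antigens and groups cytokine producers as one positive category. That gives 4 tests if antigens are pooled and 4 x 3 = 12 if not. Uncorrected and independent, the familywise error is 1 - 0.95^4 = 19% to 1 - 0.95^12 = 46%.

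**The case against.** Four stronger readings are tempting, and the article does not support them.

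- **That the ANOVA has no interaction.** The article does not say main effects only. An ANOVA naming both factors in a four-group design could carry the product term or cell contrasts, and the full protocol and SAP are not shown. What can be said is that none is specified. A joint or combined effect could also mean UP against W; only the interplay claim clearly points to interaction. A main-effects fit with equal cells also has a legitimate meaning, as the effect of each factor averaged over the other. It misleads only if read as a simple effect.
- **That the nutrition effect stays confounded.** Gender is a named term, and strong confounders are nearly always selected. Even in the four-confounder cases forward selection removes much of the bias (0.30 to 0.12, 0.40 to 0.11, 0.60 to 0.03). The harm is partial.
- **That controls come from better-off homes.** Study population says that, where a home's eligible contacts do not share an arm, "any malnourished HHC screened is enrolled to limit selection bias". It says nothing of the circumstances of control households.
- **That 48 separate T-cell tests are planned.** Multiplying subsets, cytokines and antigens ignores the grouping of cytokine producers. PD1, Treg and other cytokine analyses may add tests, but readouts from the same cells are correlated, which lowers the error rate below the independence figure.

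It is also fair that the study is labelled exploratory, that Kruskal-Wallis is only a fallback, and that Bonferroni is strict where applied. These points lower the stakes. They do not defend choosing confounders by p-value in non-randomised arms, which is a stated rule and not a detail left to another document.

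**Conclusion.** The point holds in this limited form. The stated covariate rule can leave partial residual confounding of the nutrition effect and raise its type I error. The size runs from almost nothing (one strong confounder) through 6-8% (one weak) to 9-14% (four weak-to-moderate, all acting the same way), against about 5% with prespecified covariates. These figures rest wholly on assumed confounder strengths, SD and entry threshold. The direction follows from the rule itself.

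That the Kruskal-Wallis fallback loses all adjustment and the factorial structure is certain wherever it is used. The missing contrast is a failure to specify, not proof that no interaction will be fitted. It matters because the article advertises the answer while 30 per cell can reliably detect only an interaction of about 1.0 SD. Conditional multiplicity control is a lesser weakness, worth 19-46% familywise error for 4 to 12 independent tests.

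**What to change.** - Replace forward selection, in both the ANOVA and the Poisson model, with a fixed covariate set chosen on subject-matter grounds from data already collected, for example age, sex, socio-economic index, smoking and alcohol.
- Name the nutrition-by-parasite contrast. Report it with its confidence interval, together with the simple effects U-W, WP-W and UP-W. State that 80% power at two-sided 5% is reached only for an interaction of about 1.0 SD, so a non-significant result is not evidence of additivity.
- For skewed data keep the same adjusted model on a log or rank scale in place of Kruskal-Wallis. Fix the scale in advance, because an interaction depends on it.
- Apply multiplicity control within the T-cell and cytokine family without condition. Bonferroni or the 5% false discovery rate already used for RNA sequencing would serve; the choice is secondary.

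The cost is wording and a few degrees of freedom. With each example covariate as one term, the model has 9 parameters (intercept, nutrition, parasite, their product and five covariates), leaving 120 - 9 = 111 residual degrees of freedom. No new data or participants are needed.
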